### Anesthesia protocol

2.4

Standard monitoring will include electrocardiography, pulse oximetry, and noninvasive blood pressure. General anesthesia will be initiated using intravenous administration of propofol (2 mg/kg), sufentanil (0.5 μg/kg), and rocuronium (0.6 mg/kg). Mechanical ventilation will be administered in volume-controlled mode with an inspiratory to expiratory ratio of 1:2, a respiratory rate of 10–12 breaths per minute, and a tidal volume of 6–8 mL per kg of predicted body weight. End-tidal CO_2_ levels will be kept between 35 and 45 mmHg. Anesthesia will be sustained using continuous infusions of remifentanil (0.05–0.15 μg⋅kg^–1^⋅min^–1^) and propofol (50–100 μg⋅kg^–1^⋅min^–1^), supplemented with intermittent rocuronium boluses (0.2 mg⋅kg^–1^) as needed. The ConView anesthesia consciousness monitor (Model YY-105, Zhejiang Puke Medical Technology Co., Ltd., China) will be utilized to evaluate anesthetic depth. This apparatus produces the anesthesia consciousness index (Ai), a quantitative metric derived from the analysis of frontal EEG signals. The Ai scale spans from 0, representing the deepest level of anesthesia, to 100, indicating full wakefulness. This scale exhibits high reliability and a significant correlation with the bispectral index (BIS) (21). Throughout the surgical procedure, the anesthesia consciousness index (Ai) will be maintained within the range of 40–60. Extubation will be performed when patients demonstrate regular spontaneous respiration, adequate minute ventilation, and the ability to follow commands. Patients are transferred to the post-anesthesia care unit (PACU) when their Steward Recovery Score is 5 or above. Upon arrival in the PACU, patient-controlled analgesia (PCA) will be initiated using a consistent regimen: sufentanil at a dosage of 1.5 μg/kg combined with tropisetron 6 mg in 100 mL of normal saline, administered via an electronic PCA pump. The pump settings will be programmed as follows: a continuous background infusion rate of 2 mL/h, a PCA bolus dose of 1 mL, and a lockout interval of 15 min. Rescue analgesia will be standardized such that patients with a Numeric Rating Scale (NRS) pain score greater than 5 at rest will receive intravenous flurbiprofen 50 mg as an additional analgesic. To minimize environmental confounding, all participants will be admitted to a single, dedicated gynecology ward unit following surgery. This unit features uniform room configurations (two beds per room, standardized layout), consistent lighting protocols (lights out at 22:00, dimmed night lighting), and noise control policies (designated quiet hours 22:00–06:00). The same nursing team, trained in ERAS protocols, will provide postoperative care to all participants, ensuring consistency in care delivery, visitor management, and nighttime disturbance patterns.

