## Introduction

1

Postoperative sleep disturbance (POSD) is observed in up to 62% of patients undergoing gynecologic laparoscopy, representing a substantial clinical burden (1, 2). This condition typically manifests on the first postoperative night and may persist for several days, significantly contributing to serious complications including chronic pain (3), delirium (4), cardiovascular events (5), and delayed recovery in Enhanced Recovery After Surgery (ERAS) pathways (6). The pathophysiology of POSD may be attributed to a multifactorial etiology, encompassing the disruption of the sleep-wake cycle due to the administration of general anesthetics, in conjunction with inflammation induced by surgical trauma and heightened sympathetic activity (7). These factors collectively contribute to postoperative reductions in rapid eye movement (REM) sleep, slow-wave sleep, and result in sleep fragmentation (5).

Current mainstay treatments rely primarily on pharmacological interventions such as dexmedetomidine (8), melatonin, and zolpidem (9); however, their routine use is limited by adverse effects including respiratory depression, hypotension, bradycardia, and delirium (10). Non-pharmacological interventions such as earplugs, eye masks, relaxation training, music therapy, and aromatherapy have been attempted to improve POSD (11). However, the efficacy of these methods varies considerably, and the quality of available evidence is generally low. In recent years, brain function modulation techniques, as emerging non-invasive neuromodulation approaches, have shown potential in ameliorating POSD. Du et al. found in a randomized, double-blind, sham-controlled trial that a single session of prefrontal transcranial alternating current stimulation significantly reduced the incidence of POSD on the first day after gynecological laparoscopic surgery (12). Nevertheless, this method still has certain limitations, including high equipment cost, complex operation procedures, and possible adverse reactions, which limit its widespread clinical adoption. Consequently, there is a critical demand for therapies that are safe, effective, well-tolerated, and easily implemented to enhance postoperative sleep quality.

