
### EEG power spectrum processing

2.5

Frontal quantitative EEG parameters will be obtained using the ConView YY-105 anesthesia depth monitoring system, employing bilateral frontal electrodes at a sampling rate of 500 Hz. EEG power spectral density will be estimated using the multitaper method (15 tapers, time-half bandwidth product = 8) with a 4-s window length and 50% overlap (2-s step), implemented in MATLAB’s pmtm function. The bandpass filter (0.5–45 Hz) will be applied as a zero-phase filter using forward-reverse filtering to avoid phase distortion. Artifact-free epochs will be extracted at six predetermined time points: T0 (pre-stimulation baseline): 5 min prior to the first taVNS session; T1 (preoperative sustained stimulation), 20–30 min following the initiation of taVNS; T2 (post-induction), 5 min after tracheal intubation; T3 (intraoperative maintenance), 20 min subsequent to the skin incision; T4 (peri-extubation), at the conclusion of surgery, immediately preceding emergence from anesthesia; and T5 (postoperative sustained stimulation), 20–30 min after the initiation of postoperative taVNS.

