### Data collection and management

2.9

Outcome and safety variables will be systematically collected across three distinct phases: preoperative, intraoperative, and postoperative. During the preoperative phase, demographic data, medical history, surgical information, laboratory values, and baseline assessments, including AIS, HADS, NRS for pain, and QoR-15, will be recorded at the enrolment visit immediately preceding the initial taVNS session. In the intraoperative phase, data on the duration of anesthesia and surgery, tracheal intubation time, estimated blood loss, fluid infusion volume, medication administration, and continuous EEG parameters will be meticulously documented. Postoperatively, the AIS and HADS will be assessed in the evenings of POD 1, 2, and 3. Additionally, the QoR-15 and NRS pain scores, both at rest and during movement, will be evaluated on the morning of POD 1, alongside the documentation of clinical outcomes and any adverse events.

All data will be systematically recorded using standardized case report forms (CRFs) and subsequently double-entered into an encrypted electronic database by two independent research assistants. A random sample comprising 10% of the CRFs, stratified according to the enrolment sequence, will undergo verification against the original medical records. The data manager will be responsible for generating queries related to missing or inconsistent values, with the principal investigator overseeing their resolution. In compliance with institutional policy and ICH-GCP guidelines, original CRFs will be securely stored in a locked cabinet with restricted access for a minimum duration of 5 years. The electronic data will be hosted on hospital servers, safeguarded by SSL encryption, automated backups, and role-based access control, ensuring access is limited to authorized study personnel.

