### Statistical analysis

2.11

Statistical analyses will be performed using SPSS Statistics 26.0 (IBM Corp.) and R 4.4.0 (R Foundation). MATLAB R2018b (MathWorks, Natick, MA) will be employed for the preprocessing and spectral analysis of EEG data. Normality will be assessed using the Shapiro-Wilk test and Q-Q plots. Continuous variables will be presented as mean ± standard deviation or median (interquartile range), and categorical variables will be shown as frequencies and percentages.

The primary outcome (incidence of AIS ≥ 6 on POD 1) will be analyzed using the chi-square test to compare proportions between the taVNS and sham groups. The effect size will be expressed as an absolute risk reduction with a 95% confidence interval. Linear mixed-effects models will analyze repeated measures, including (1) AIS total scores (Pre 1 to POD 3); (2) HADS-A and HADS-D (as two separate scales, Pre 1 to POD 3); (3) objective sleep parameters from actigraphy; and (4) EEG spectral power across five bands (delta, theta, alpha, beta, and gamma) at six time points (T0–T5). Models include fixed effects for group, time, group × time interaction, and random intercepts for subjects. For repeated clinical outcomes, Bonferroni correction will be applied across four key endpoints: HADS-A, HADS-D, AIS trajectory, and objective sleep parameters from actigraphy, yielding a significance threshold of α = 0.0125 (0.05/4). For EEG spectral analyses, given the exploratory nature and high dimensionality (5 frequency bands × 6 timepoints), the Benjamini–Hochberg procedure will control the false discovery rate at q < 0.05.

A three-step approach will be used to identify predictors of POSD: (1) Univariate screening (*P* < 0.10) for 30 EEG variables (5 bands × 6 timepoints); (2) LASSO regularization (10-fold CV) to select independent predictors; (3) Multivariable logistic regression reporting ORs and 95% CIs.

The main analysis will adhere to the intention-to-treat methodology. To address missing data, multiple imputation via chained equations will be utilized, generating 20 imputations under the assumption that data are missing at random. Sensitivity analyses will incorporate pattern-mixture models to account for mechanisms where data are missing not at random. The per-protocol analysis will exclude cases with significant protocol deviations. Effect sizes will be reported as Cohen’s d, alongside 95% confidence intervals.

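### Anesthetic infusions are titrated to an index from the same frontal EEG that is the outcome, so a null at T3–T4 is ambiguous, and the POSD predictor model omits anesthetic dose

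*Protocol article*

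**What the plan says.** **Titration.** Section 2.4 (Anesthesia protocol) describes the ConView YY-105 monitor: "This apparatus produces the anesthesia consciousness index (Ai), a quantitative metric derived from the analysis of frontal EEG signals". It then sets the target: "Throughout the surgical procedure, the anesthesia consciousness index (Ai) will be maintained within the range of 40–60". Maintenance is by propofol at 50–100 μg/kg/min and remifentanil at 0.05–0.15 μg/kg/min. Induction doses are fixed per kilogram.

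**Outcome EEG.** Section 2.5 names the same device: "Frontal quantitative EEG parameters will be obtained using the ConView YY-105 anesthesia depth monitoring system". Of the six timepoints, three fall under anesthesia: "T2 (post-induction), 5 min after tracheal intubation"; "T3 (intraoperative maintenance), 20 min subsequent to the skin incision"; and T4, at the end of surgery before emergence. T0 and T1 precede induction, and T5 follows extubation.

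**Analysis.** Section 2.11 gives the mixed model for EEG power fixed effects for group, time and their interaction, with a random intercept. The search for POSD predictors starts with univariate screening "for 30 EEG variables (5 bands × 6 timepoints"), then uses LASSO to pick independent predictors, then multivariable logistic regression. Neither analysis lists anesthetic dose or Ai.

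**Dose.** Section 2.9 says that intraoperative "medication administration, and continuous EEG parameters will be meticulously documented", so dose is recorded. The Introduction lists among the causes of POSD "the disruption of the sleep-wake cycle due to the administration of general anesthetics".

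**The concern.** The outcome signal sits inside a control loop. If the first taVNS session shifts cortical state enough to move Ai, blinded staff holding Ai in range may change the infusion. Part of the effect then appears as a dose difference and not as an EEG difference. No planned analysis looks at dose, so it would go unseen there.

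Two readings are at stake.

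- **A null group difference at T3 or T4** could be taken as evidence that taVNS does not act on the intraoperative cortex. The Discussion rests its mechanistic premise on intraoperative EEG being modifiable, and expects the EEG data to be informative even if the trial is null.
- **An EEG–POSD association at T2–T4** could be reported as an oscillatory biomarker when it only marks how much anesthetic the patient received.

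**Working it through.** **1. The plan's own design figure.** The protocol gives no effect size or SD for EEG, so there is no EEG figure to reproduce. Its only design calculation is for the primary outcome (section 2.10: 0.45 versus 0.20, two-sided α 0.05, power 0.80). With unpooled variance:

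n = (1.960 + 0.842)² × (0.45×0.55 + 0.20×0.80) / 0.25² = 7.849 × 0.4075 / 0.0625 = 51.2, so 52 per arm.

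52 / 0.90 = 57.8, so 58 per arm and 116 in total. This matches the plan. The present point does not depend on it, but 52 per arm is used below.

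**2. Which timepoints are affected.**

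| Timepoint | State | Ai-titrated? |
|---|---|---|
| T0, T1 | before induction | no |
| T2 | 5 min after intubation | mainly reflects fixed per-kg induction doses; the Ai target is stated for surgery |
| T3 | 20 min after incision | yes |
| T4 | end of surgery | yes, as far as titration continues |
| T5 | after extubation | no; residual drug is possible |

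Recorded under anesthesia: 3 timepoints × 5 bands = 15 of 30 candidate predictors. T3 and T4 alone give 2 × 5 = 10 of 30.

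**3. Room for dose to move.** Propofol: 100/50 = 2-fold. Remifentanil: 0.15/0.05 = 3-fold. The text does not say which drug is adjusted to hold Ai. That it is these infusions is an inference from their being given as ranges.

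**4. Illustration of the offset (assumptions not in the protocol).** Take Ai at fixed dose as normal with mean 50 in sham. Let taVNS lower it by 5 or 10 points, and let titration return any value outside 40–60 to the nearest limit. Simulation with 200,000 patients per arm gives the share of the Ai shift still visible:

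| Assumed SD of Ai | Shift 5 | Shift 10 |
|---|---|---|
| 5 | 0.92 | 0.80 |
| 10 | 0.67 | 0.61 |
| 15 | 0.49 | 0.46 |

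The shift is reduced, not removed. Individual band powers are held less directly than Ai, so these shares do not carry over to them.

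**5. What attenuation would do to power.** For one timepoint, 52 per arm, two-sided 0.05, no false-discovery correction, and an assumed true standardized difference d = 0.5: power ≈ Φ(d√(n/2) − 1.96).

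- No attenuation: Φ(0.5×5.099 − 1.96) = 72%.
- 25% attenuation (d = 0.375): 48%.
- 50% attenuation (d = 0.25): 25%.

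**6. Events available to the predictor model.** 52×0.45 + 52×0.20 = 23.4 + 10.4 = 33.8, about 34 POSD cases at the planning rates. This limits how many dose terms can be added.

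**7. Why confounding belongs to the predictor model only.** Dose acts on the EEG and, by the Introduction's account of anesthetics, may act on POSD. In the EEG–POSD association it is therefore a possible common cause. In the randomized comparison, a dose difference caused by taVNS arises after allocation and lies on the pathway.

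**The case against.** The best case against the point is that the EEG analyses are labelled exploratory and false-discovery controlled, and that the Introduction ties spectral modulation to the stimulation periods, which are T1 and T5. A common depth target is also a defensible design, because it removes noise from differing depth. Covariates of an exploratory model are often left to the SAP, and an EEG variable that tracks dose can still predict. All of this limits the point. It does not dispose of it: section 2.11 does fix the candidate set and the promotion of survivors to independent predictors, and false-discovery control does not address confounding.

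A reader might infer three stronger things that the protocol does not support.

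- **That the mechanism objective cannot be read.** T1 versus T0 is free of anesthetic, and T5 is not Ai-titrated.
- **That the T2–T4 group contrast is confounded by dose.** Arms are randomized and anesthesia providers blinded; dose is a consequence of allocation, not a confounder of it.
- **That titration holds the arms' EEG equal at T2–T4.** T2 mainly reflects induction doses, and Ai 40–60 is a 20-point band on one summary index. Five band powers can differ at the same Ai.

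The protocol also nowhere says that a null at these timepoints will be read as no modulation. The gap is that it gives no means of interpreting one.

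**Conclusion.** The point holds in a limited form. At T3, and at T4 as far as titration continues, the group contrast estimates the total effect of taVNS under index-guided anesthesia. A null there is not evidence against direct cortical modulation. In the predictor analysis, 15 of 30 candidates are open to confounding by anesthetic dose, most plausibly the 10 at T3 and T4, where infusion rates vary.

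The size of either effect cannot be computed from the protocol. The 46–92% retained Ai shift and the fall in power from 72% to 48% or 25% are illustrations under assumed inputs. The confounding argument also assumes that POSD risk varies with anesthetic dose, whereas the Introduction speaks only of anesthetic administration. The primary endpoint, the sample size and the clinical secondary outcomes are unaffected.

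**What to change.** 1. Name T1 versus T0 and T5 as the main mechanistic contrasts, noting possible residual drug at T5.
2. Report Ai and the recorded propofol and remifentanil dose by arm beside T2–T4 band power, and read them together. Do not adjust the main treatment contrast for dose. Label any dose-adjusted contrast a mediation-type sensitivity analysis.
3. Include recorded anesthetic dose in the predictor model before calling a T2–T4 EEG variable an independent predictor. Keep it to one or two terms, or penalize them, given about 34 expected events.
4. Add to the limitations that a null at T3–T4 under Ai titration does not show absence of cortical modulation.

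The cost is analysis-plan wording, a table or two from data already recorded, a slightly larger exploratory model and more cautious T2–T4 claims. Anesthetic management does not change.

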
### EEG power spectrum processing

2.5

Frontal quantitative EEG parameters will be obtained using the ConView YY-105 anesthesia depth monitoring system, employing bilateral frontal electrodes at a sampling rate of 500 Hz. EEG power spectral density will be estimated using the multitaper method (15 tapers, time-half bandwidth product = 8) with a 4-s window length and 50% overlap (2-s step), implemented in MATLAB’s pmtm function. The bandpass filter (0.5–45 Hz) will be applied as a zero-phase filter using forward-reverse filtering to avoid phase distortion. Artifact-free epochs will be extracted at six predetermined time points: T0 (pre-stimulation baseline): 5 min prior to the first taVNS session; T1 (preoperative sustained stimulation), 20–30 min following the initiation of taVNS; T2 (post-induction), 5 min after tracheal intubation; T3 (intraoperative maintenance), 20 min subsequent to the skin incision; T4 (peri-extubation), at the conclusion of surgery, immediately preceding emergence from anesthesia; and T5 (postoperative sustained stimulation), 20–30 min after the initiation of postoperative taVNS.

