**FIGURE 1 F1:**
[figure not shown]
Flowchart of the study design.

**TABLE 1 T1:** Study schedule for data measurements.

Study period											
	Enrollment	Allocation	Post allocation								
Timepoint	Pre1	0 d	T0	T1	T2	T3	T4	T5	POD 1	POD 2	POD 3
Enrollment											
Eligibility screen	X										
Informed consent	X										
Random allocation		X									
Interventions											
Active taVNS				X				X			
Sham taVNS				X				X			
Assessments											
Baseline data	X	X									
EEG			X	X	X	X	X	X			
AIS	X								X	X	X
HUAWEI WATCH GT2	X								X	X	X
QoR-15	X								X		
NRS	X								X		
PSQI	X										
HADS-A	X								X	X	X
HADS-D	X								X	X	X
Adverse events	Record at any time at any time at any time										

Pre1 for preoperative day 1, T0, preoperative baseline (5 min before taVNS); T1, preoperative sustained stimulation period (20–30 min taVNS); T2, post-induction (5 min after intubation); T3, intraoperative maintenance (20 min after incision); T4, peri-extubation (end of surgery); T5, postoperative sustained stimulation (20–30 min post-taVNS). POD 1–POD 3 for postoperative days 1–3; taVNS, transcutaneous auricular vagus nerve stimulation; EEG, electroencephalography; AIS, Athens Insomnia Scale; QoR-15, 15-item Quality of Recovery questionnaire; NRS, numeric rating scale; PSQI, Pittsburgh Sleep Quality Index; HADS-A/HADS-D, Hospital Anxiety and Depression Scale-Anxiety/Depression subscale.

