### Study interventions

2.6

The interventions will be administered at two specific time points: 30 min before the induction of anesthesia and 5 min after tracheal extubation in the PACU, with each session lasting 30 min. Prior to the initiation of stimulation, the left auricle will be cleansed using gauze moistened with a saline solution. The unblinded coordinator will position the taVNS device (model taVNS501, Reshen Medical Technology Co., Ltd., Changzhou, China) according to the randomization assignment.

Participants assigned to the taVNS group will undergo stimulation at the left cymba conchae, an area innervated by the auricular branch of the vagus nerve. This stimulation will be administered using a pulse frequency of 20 Hz and a pulse width of 250 μs. The stimulus amplitude will initially be set to zero and will be gradually increased until the participant experiences a tolerable tingling sensation, typically within 30 s, which will be maintained throughout the 30-min session. In the sham group, the electrode placement will be identical to those of the active taVNS group using the same stimulation parameters. The stimulus amplitude will be incrementally increased until the participant perceives a tingling sensation after which the current will be immediately discontinued. The device will remain powered on, with identical auditory and visual cues, for the entire 30-min session to ensure the absence of sustained neuromodulatory effects while preserving participant blinding.

During each stimulation, participants will remain in a supine position while undergoing continuous monitoring through electrocardiography, pulse oximetry, and noninvasive blood pressure assessment. Trained personnel will provide constant observation of the participants. Stimulation will be immediately stopped if any of the following occur: (1) unbearable discomfort; (2) oxygen saturation (SpO_2_) drops below 90%; (3) heart rate falls below 50 beats per minute or decreases by more than 20% from the initial rate; (4) a new arrhythmia begins; (5) hemodynamic instability, defined as systolic blood pressure below 90 mmHg or above 180 mmHg; or (6) any significant adverse event. The attending physician will decide on the suitable clinical management.

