#### Secondary outcomes

2.7.2

Trajectory of Postoperative Sleep Quality (1) Subjective sleep quality: The trajectory of AIS total scores from Preoperative Day 1 (Pre-1) through POD 3. (2) Objective sleep parameters: Wrist actigraphy (HUAWEI WATCH GT2) measured continuously from Pre-1 through POD 3. Metrics include sleep continuity (latency, awakenings, wake after sleep onset, efficiency, and total sleep time) and sleep architecture (duration of light, deep, and REM sleep).Anxiety and Depression The Hospital Anxiety and Depression Scale (HADS) will evaluate anxiety (HADS-A) and depression (HADS-D) at Pre-1, POD 1, POD 2, and POD 3. Each subscale comprises seven items scored 0–3; scores ≥ 8 indicate probable anxiety or depression (23).Postoperative Pain and Recovery Quality Pain intensity will be assessed using the Numeric Rating Scale (NRS, 0–10) at rest and during movement on POD 1 (24). Analgesic consumption and patient-controlled analgesia demands will be recorded. Recovery quality will be evaluated on POD 1 using the 15-item Quality of Recovery (QoR-15) questionnaire (scores 0–150, higher scores indicating better recovery) (25).Quantitative EEG Parameters (1) Absolute power: The integral of the power spectral density (PSD) over respective frequency bands (delta 1–4 Hz, theta 4–8 Hz, alpha 8–12 Hz, beta 12–25 Hz, and gamma 25–45 Hz). (2) Peak frequency: The frequency at which maximum PSD occurs within each band.

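### The multitaper settings are too coarse for the delta, theta and alpha bands, and T1/T5 beta and gamma are open to 20 Hz stimulation pickup in the active arm only

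*Protocol article*

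**What the plan says.** Section 2.5 specifies a "multitaper method (15 tapers, time-half bandwidth product = 8) with a 4-s window length and 50% overlap (2-s step"), recorded "employing bilateral frontal electrodes at a sampling rate of 500 Hz" and band-passed at 0.5–45 Hz. Section 2.7.2 lists two quantitative EEG outcomes among the secondary outcomes. One is absolute power in "delta 1–4 Hz, theta 4–8 Hz, alpha 8–12 Hz, beta 12–25 Hz, and gamma 25–45 Hz". The other is "Peak frequency: The frequency at which maximum PSD occurs within each band".

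On timing, section 2.5 defines "T1 (preoperative sustained stimulation), 20–30 min following the initiation of taVNS" and defines T5 in the same way from the start of the postoperative session. Section 2.6 says each session lasts 30 min. The active arm is stimulated "using a pulse frequency of 20 Hz" for the whole session. In the sham arm the amplitude is raised until tingling is felt, "after which the current will be immediately discontinued". The Table 1 footnote words the last timepoint differently: "T5, postoperative sustained stimulation (20–30 min post-taVNS").

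Section 2.11 calls the EEG spectral analyses exploratory, with false discovery rate control. It also enters 30 EEG variables (five bands at six timepoints) into the screen for POSD predictors.

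**The concern.** There are two separate problems.

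**Resolution.** A multitaper estimate averages power over a span set by the time-half-bandwidth product and the window length. If that span is as wide as the band, power near an edge is credited to the neighbouring band. The frequency of the maximum inside the band then reflects the smoothing and the background slope as well as the rhythm.

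**Stimulation pickup.** At T1 and T5 the current is on in one arm and off in the other. The stimulation frequency lies in beta and its second harmonic, 40 Hz, lies in gamma. An electrical line from the stimulator would therefore appear in the active arm only. Randomisation gives no protection, because the artefact comes with the assigned treatment, and false discovery control does not correct bias.

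At stake is the mechanistic reading of the trial. Pickup could be reported as taVNS changing beta or gamma power. It could also enter the predictor screen through T1 and T5 band power. There it would act partly as a marker of treatment arm, since the stated steps list EEG variables only.

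**Working it through.** **Inputs.** Time-half-bandwidth product NW = 8, K = 15 tapers, window T = 4 s and sampling rate 500 Hz (section 2.5); band limits (section 2.7.2); stimulation at 20 Hz (section 2.6).

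**The plan's own figure.** The usual taper count is K = 2·NW − 1 = 2×8 − 1 = 15. This matches the stated 15, so the settings agree with each other and are not a misprint.

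**Bandwidth.** W = NW/T = 8/4 = 2 Hz, so the full span is 2W = 4 Hz.

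| Band | Width (Hz) | 4 Hz span / width |
|---|---|---|
| Delta | 3 | 1.33 |
| Theta | 4 | 1.00 |
| Alpha | 4 | 1.00 |
| Beta | 13 | 0.31 |
| Gamma | 20 | 0.20 |

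**Leakage.** As a hand approximation, a tone at distance d from an edge (d < 2 Hz) leaks (2 − d)/4. This gives 37.5% at 0.5 Hz and 25% at 1 Hz. Exact computation with the DPSS tapers (2,000 samples per window) agrees:

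- 3 Hz tone: about 24% falls in theta.
- 8.5 Hz tone: about 37% falls in theta.
- 11 Hz tone: about 24% falls in beta.
- 6 and 10 Hz tones (mid-band): 1% or less leaks.

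With NW = 2 and K = 3 on the same window, W = 2/4 = 0.5 Hz. The 8.5 Hz leak falls to between 0.5% and 1.1% across the runs, and the 3 Hz leak to about 0.2% or less.

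**Peak frequency.** The documents give no spectrum, so the inputs here are assumed. The first case has background amplitude proportional to 1/f and a narrow alpha peak (SD 0.5 Hz, amplitude twice the background). True peaks at 9, 10 and 11 Hz are read at 8.06, 8.61 and 9.55 Hz under the plan, and at 8.99, 10.02 and 10.96 Hz with NW = 2. A broader peak (SD 1 Hz) at five times a 1/f power background is read at 8.85, 9.95 and 10.92 Hz under the plan. Over the range of peak width, height and slope tried, the downward bias ran from about 0.1 to 2.9 Hz.

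**Stimulation line.** T1 and T5 in section 2.5 cover minutes 20–30 of a 30-min session, so the active-arm current is on throughout. Both 20 and 40 Hz pass the 0.5–45 Hz filter. At W = 2 Hz they spread over 18–22 and 38–42 Hz, and 99.9% of each stays inside beta or gamma. Narrower tapers alone do not change that.

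Pickup size is not given. For a sinusoid of amplitude a on a beta background of RMS b, the power ratio is 1 + (a²/2)/b². With b assumed at 2 to 5 µV:

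| a (µV) | b = 2 | b = 3 | b = 5 |
|---|---|---|---|
| 1 | 1.12 | 1.06 | 1.02 |
| 5 | 4.12 | 2.39 | 1.50 |
| 10 | 13.5 | 6.56 | 3.00 |

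**Why the two repairs belong together.** Omitting 19–21 Hz removes about 53% of a 20 Hz line at the planned bandwidth, but 99.7% at NW = 2.

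**The case against.** The settings are internally consistent, and trading resolution for low variance is a legitimate choice. Every arm and timepoint uses the same estimator, so smearing cannot by itself produce a group or group-by-time effect. Mid-band theta and alpha power is largely kept, and beta and gamma are wide enough to be little affected. All of this stands and limits the first problem to band-edge power and peak frequency in delta, theta and alpha.

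A reader might infer that peak frequency is always pulled to the band edge, or cannot be recovered at all. The simulations do not support that: a broad, strong alpha peak is read within about 0.2 Hz.

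A reader might also infer that T1/T5 beta and gamma results will be wrong. The documents do not show that. They give no pickup amplitude, and an artefact-removal step may sit in the full protocol. What remains is that the timing is stated, and that the safeguard stated, choosing artefact-free epochs, cannot remove a line present in every active-arm epoch.

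Masking also has a price: it would delete any true 20 or 40 Hz neural response. That is a fair reason to run it as a sensitivity analysis rather than as the only analysis.

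The T5 wording in Table 1 may be only a loose label, since the same entry speaks of sustained stimulation. But one reading has the current on and the other has it off, so it is worth settling.

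**Conclusion.** The point holds in limited form. The ±2 Hz half-bandwidth follows exactly from the stated settings and needs no assumption. The leakage figures (about 37% at 0.5 Hz and 24% at 1 Hz from an edge) follow from it for pure tones. The peak-frequency bias is real, but its size depends on assumed peak shape and background.

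The arm-specific exposure at T1 and T5 follows from sections 2.5 and 2.6. Whether it produces a material artefact is open, because the result runs from negligible to several-fold inflation over the amplitudes assumed. T0 and T2–T4 are recorded without stimulation and are not exposed.

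Peak frequency is not among the 30 predictor variables, so the predictor screen is touched through band power only. The EEG analyses are declared exploratory, and the primary endpoint, AIS ≥ 6 on POD 1, is unaffected. The plan should be changed on this point, but the trial's main conclusion does not depend on it.

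**What to change.** 1. Use a narrower bandwidth on the same 4-s windows, for example NW = 2 with 3 tapers (±0.5 Hz), and average over windows to hold the variance down. One minute of clean EEG at a 2-s step gives (60 − 4)/2 + 1 = 29 windows.
2. In both arms and at all six timepoints, omit 19–21 and 39–41 Hz from the beta and gamma integrals and from the peak search, at least as a sensitivity analysis. Do this together with step 1, because the mask works poorly at the planned bandwidth.
3. State that group differences in beta or gamma at T1 or T5 will not be interpreted as neural unless they persist after masking or in data recorded with the current off.
4. Make the T5 definition the same in Table 1 and section 2.5.

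**Cost.** This is a parameter change in the analysis script and a few lines of text; the raw recordings are unaffected. Single-window spectra become noisier before averaging. The mask gives up 2 of 13 Hz in beta (15%) and 2 of 20 Hz in gamma (10%), including any genuine response at 20 or 40 Hz. Relying on current-off data would describe the period after stimulation rather than sustained stimulation, and the report should say so.
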